## Abstract

INTRICATE is a prospective double-blind placebo-controlled feasibility study, assessing the influence of combined vitamin K2 and vitamin D3 supplementation on micro-calcification in carotid artery disease as imaged by hybrid Sodium [^18^F]Fluoride (Na[^18^F]F) positron emission tomography (PET)/ magnetic resonance imaging (MRI). Arterial calcification is an actively regulated process and results from the imbalance between calcification promoting and inhibiting factors. Considering the recent advancements in medical imaging, ultrasound (US), PET/MRI, and computed tomography (CT) can be used for the selection and stratification of patients with atherosclerosis. Fifty-two subjects with asymptomatic carotid artery disease on at least one side of the neck will be included in the study. At baseline, an Na[^18^F]F PET/MRI and CT examination will be performed. Afterwards, subjects will be randomized (1:1) to a vitamin K (400 µg MK-7/day) and vitamin D3 (80 µg/day) or to placebo. At the 3-month follow-up, subjects will undergo a second Na[^18^F]F PET/MRI and CT scan. The primary endpoint is the change in Na[^18^F]F PET/MRI (baseline vs. after 3 months) in the treatment group as compared to the placebo arm. Secondary endpoints are changes in plaque composition and in blood-biomarkers. The INTRICATE trial bears the potential to open novel avenues for future large scale randomized controlled trials to intervene in the plaque development and micro-calcification progression.

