### 4.3. Statistical Analyses Plan

Our null hypotheses states that MK-7 and vitamin D3 do not influence the change (i.e., progression) of micro-calcifications in 3 months of supplementation when compared to a placebo; there will be no difference in the degree of calcification between the MK7+D3 group vs. the placebo at the end of the study. Our alternative hypothesis states that MK-7 and vitamin D3 have a greater effect on the change of micro-calcification in 3 months of supplementation compared to placebo.

The descriptive statistics for each variable at baseline will be presented for both groups combined and individually (i.e., MK7+D3 and placebo) for each of the following parameters: mean, standard deviation of the variable, standard error of the mean, range (minimum-maximum), median, quartiles, and confidence intervals where necessary. Descriptive statistics for variables at the end of the study will be presented separate for both groups (i.e., MK7+D3 and placebo).

Both intention-to-treat and per protocol analysis will be performed. For the intention-to-treat analysis, all randomized subjects (with data available from the end of the study visit) will be included. In the per protocol analysis, only subjects who fully complied with the prescribed supplementation will be included.

The main outcome parameter (i.e., the longitudinal change time of micro-calcification as measured by the Na[^18^F]F uptake via hybrid PET/MRI) will be presented as a continuous variable. It will be expressed as a mean difference (i.e., the standard uptake value and target-to-background radio of Na[^18^F]F at the end of the study visit minus Na[^18^F]F maximal uptake at baseline). To investigate the existence of significant predictor(s) for the main outcome parameter (i.e., the longitudinal change of micro-calcification), univariate analysis will be used. If the significance level (i.e., α) will be between 5% and 25% at the univariate *t*-test hypothesis testing (i.e., *p* > 0.05 and *p* < 0.25), a multivariate analysis will be used, in order to investigate a possible association or interaction between variables.

In order to decide to either reject or accept our null hypothesis, a two-sided confidence interval using 95% confidence will be calculated and reported. A two-sided hypothesis test using a significance level (i.e., α) of 5% will also be reported.

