The CAC score and the US data will be presented as continuous variables. Their longitudinal change will be also expressed as a mean difference (i.e., value at the end of the study visit minus value at baseline) and will be presented as continuous variables.

For the continuous data including age, blood pressure, body-mass index, lipid-rich necrotic volume, normalized wall index, dp-ucMGP, and other laboratory tests, the distribution of variables will be analyzed (verification of normality of distribution for all subjects) by histograms. To investigate the existence of significant predictor(s) for the secondary outcome parameters, univariate analysis will be used. If the significance level (i.e., α) will be between 5% and 25% at the univariate t-test hypothesis testing (i.e., *p* > 0.05 and *p* < 0.25), a multivariate analysis will be used, in order to investigate a possible association or interaction between variables. If variables display no normal distribution, data will be transformed using appropriate transformations. If transformation is not possible, this data is analyzed by non-parametric statistical tests (i.e., Chi-square test).

Baseline parameters will be presented: sex, age, bodyweight, length, body-mass index, medical history, medication, family history, and cardiovascular risk factors.

Health status and use/changes of medication will be verified during the baseline visit and at the end of the study visit.

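### The only non-parametric fallback named for continuous variables that cannot be transformed is the Chi-square test, and no grouping is given that would let it be applied

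*Protocol article*

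**What the plan says.** The second part of section 4.3 of the protocol article sets out a sequence of steps for continuous variables.

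- **Scope.** It opens with "For the continuous data including age, blood pressure, body-mass index, lipid-rich necrotic volume, normalized wall index, dp-ucMGP, and other laboratory tests". The word *including* leaves the list open.
- **Step 1.** Histograms are used to judge normality.
- **Step 2.** "If variables display no normal distribution, data will be transformed using appropriate transformations".
- **Step 3.** "If transformation is not possible, this data is analyzed by non-parametric statistical tests (i.e., Chi-square test").

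The paragraph just before this one deals with the coronary calcium score and ultrasound: "The CAC score and the US data will be presented as continuous variables". Their change is to be given as a mean difference. For the main PET outcome, section 4.3 says separately that it "will be presented as a continuous variable", with a two-sided 95% confidence interval and a two-sided 5% test.

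The article names no rank-based test anywhere, and it gives no cut-point or category for any of the listed variables.

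**The concern.** A Chi-square test takes a table of counts. A plaque volume, a wall index or a plasma concentration does not come as counts. To follow step 3, someone must decide how many groups to form and where to cut, and the plan leaves both open. That decision would come after the histograms have been inspected and transformations tried, so with the data in hand. Different cuts can give different p-values for the same secondary outcome.

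There is also a cost in sensitivity. Grouping keeps only which side of a cut each value falls on, whereas a rank test keeps the full ordering. With 52 subjects there is little information to spare. The Chi-square test itself also gives no estimate of the treatment effect in the units of measurement.

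**Working it through.** **Is there a figure to reproduce?** No. The article states 52 subjects without a derivation and gives no effect size, standard deviation or power. The check is therefore on the rule itself and on what it would cost.

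**Step 1: can the rule be carried out as written?** The scope sentence calls the variables continuous, step 3 names a test for category counts, and nothing between them turns one into the other. The rule cannot be carried out without an added choice.

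**Step 2: inputs for the cost.**

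- Sample size: "Fifty-two subjects with asymptomatic carotid artery disease on at least one side of the neck will be included in the study" (Abstract), randomized 1:1, so 52 / 2 = 26 per arm with no dropout assumed.
- Test level: "A two-sided hypothesis test using a significance level (i.e., α) of 5% will also be reported" (section 4.3, stated for the primary analysis and used here for illustration).
- Assumed, because the article gives neither: a split at the pooled median, and the location shifts below. A shift of 0.8 SD was chosen because 26 per arm gives 80% power for a t-test at about 0.78 SD.

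**Step 3: what a median split demands.** Without ties, 26 of the 52 values lie above the pooled median. If x of them are in one arm, the other arm has 26 − x.

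- Uncorrected: χ² = (2x − 26)² / 13. At x = 16, 36 / 13 = 2.77. At x = 17, 64 / 13 = 4.92. The 5% critical value is 3.84, so a split of 17 v 9 is needed.
- Continuity-corrected: χ² = (|2x − 26| − 1)² / 13. At x = 17, 49 / 13 = 3.77, not significant. At x = 18, 81 / 13 = 6.23. A split of 18 v 8 is needed.

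Under no effect, x is hypergeometric (26 drawn from 52, of which 26 are above the median). The exact chance of 17 v 9 or more extreme in either direction is 5.1%, and of 18 v 8 or more extreme 1.2%. The corrected test is thus very conservative at this size.

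**Step 4: simulated power**, 26 per arm, 8,000 trials per row.

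| Distribution and shift | Wilcoxon | Chi-square, uncorrected (loss) | Chi-square, corrected (loss) |
|---|---|---|---|
| Normal, 0.8 SD | 77.8% | 63.0% (14.8) | 41.4% (36.4) |
| Lognormal (log SD 1), 0.8 | 82.2% | 61.6% (20.6) | 40.0% (42.2) |
| Exponential, 0.5 | 70.7% | 44.3% (26.4) | 24.2% (46.5) |
| t with 3 df, 1.0 | 77.0% | 72.7% (4.3) | 50.5% (26.5) |
| Laplace, 1.0 | 82.3% | 82.9% (none) | 63.3% (19.0) |

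Losses are in percentage points. With no shift, the Wilcoxon test and the uncorrected Chi-square test both rejected in about 5% of trials, and the corrected Chi-square test in about 1%.

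**Step 5: data with many zeros.** Two scenarios, again at 26 per arm and with assumed shares of zeros:

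- Wilcoxon 37%, Chi-square 37% uncorrected (no loss) and 19% corrected (37 − 19 = 18 points).
- Wilcoxon 81%, Chi-square 73% uncorrected (8 points) and 50% corrected (81 − 50 = 31 points).

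**Step 6: large-sample benchmark.** For normal data the efficiency of the median test relative to Wilcoxon is (2/π) / (3/π) = 2/3.

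**The case against.** The strongest reply is that this is a last resort. A variable reaches it only if it is non-normal and no transformation works. A reader might infer that every non-normal outcome goes to a Chi-square test. The text does not say that, because transformation comes first.

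It follows that some rows of the table are benchmarks only. Normal data never trigger the rule, and lognormal data become normal on the log scale. Exponential data, with the largest loss, can often be transformed too. For the kinds of data more likely to be left over (symmetric heavy tails, many zeros), the uncorrected loss in these checks is between none and 8 points. This stands, and it limits what can be said about size.

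A median split followed by a Chi-square test is also a recognised procedure, Mood's median test, with its cut set by rule. It would be too strong to say that no Chi-square procedure can serve continuous data. But the plan does not name the median test or any other grouping, so the gap remains. Reading *i.e.* as a slip for *e.g.* does not help either, since the one example given would still be unsuited to ungrouped measurements.

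A reader might also infer that no effect estimate would be reported. For the calcium score and ultrasound that is not supported, because section 4.3 separately promises a mean difference. Whether those two, or hemorrhage volume, fall under the fallback at all depends on how far *including* reaches.

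Finally, a reader might object to the pooled check ("verification of normality of distribution for all subjects"). It has no practical weight. For baseline values, pooling randomized arms is harmless. For two normal arms 0.8 SD apart, skewness is zero and kurtosis is (3 + 6 × 0.4² + 0.4⁴) / (1 + 0.4²)² = 3.9856 / 1.3456 = 2.96, against 3 for a normal. A histogram of 52 values would not show that.

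**Conclusion.** The concern holds as a fault in a stated rule. For continuous variables that are non-normal and cannot be transformed, the plan names one test, that test needs groups, and no groups are defined. This reaches at least three secondary outcomes by name, plus the laboratory tests.

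The size of the harm is less certain. It rests on 26 per arm, a median split, assumed shifts and assumed shares of zeros. Under these, the power loss against Wilcoxon runs from none to about 26 points uncorrected, and from about 18 to 46.5 points with continuity correction. The article does not say whether the correction would be used.

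A reader might infer that the primary analysis is compromised. The documents do not support this: the PET outcome is not in the list and has its own interval and test. In a feasibility study, a misnamed fallback for secondary variables is of moderate severity. It should be corrected before analysis but does not threaten the main result.

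**What to change.** Replace the named fallback in section 4.3 along these lines:

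- **Comparisons between arms:** the Wilcoxon-Mann-Whitney test (with tie correction), reported with a Hodges-Lehmann estimate of the shift and its 95% confidence interval.
- **Associations between continuous variables:** Spearman correlation.
- **Categorical items such as fibrous cap status:** Chi-square or Fisher's exact test.

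State whether the rule also covers the coronary calcium score, the ultrasound measures and intra-plaque hemorrhage volume. If a grouped analysis of any continuous variable is wanted, fix its cut-points before unblinding.

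The cost is a change of wording. No subjects, visits, scans or samples are added.

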## 5. Study Procedures

An outline in chronological order, with all the procedures that will be received by the subjects, is available in Table 1.

### 5.1. Hospital Visit

At baseline visit, a complete medical interview and physical examination will be performed with emphasis on the detection of signs of cardiovascular disease (i.e., coronary and carotid artery disease). Furthermore, the height, weight, and waist-hip circumference will be measured.

Both at baseline and end of the study visits arterial blood pressure will be measured on both arms with an electronic blood-pressure measurement device. Before measurement, the subject will be seated for at least 5 min. Moreover, an ECG will be acquired.

### 5.2. Na[^18^F]F PET/MRI

The PET/MRI will be performed using a hybrid PET/MRI scanner (Siemens Biograph mMR, Siemens, Forchheim, Germany). During the PET scan (on hybrid PET/MRI scanner), MRI images will be concomitantly acquired to the PET images. A dedicated coil will be used for imaging of the carotid bifurcation. This coil allows for sub-millimeter resolution imaging of the lumen, vessel walls, and atherosclerotic plaques.

As Na[^18^F]F is eliminated by the kidneys, it will accumulate in the urinary bladder. In order to reduce the radiation exposure to the entire urinary tract, subjects will be asked to drink 0.5 L water in the hour before arrival at the hospital; for Na[^18^F]F, there is no fasting required. Upon arrival, study participants will be asked to drink an additional 0.5 L water and the procedure will be explained once more. Afterwards, 185 MBq of Na[^18^F]F will be injected via a venipuncture of the arm. Subjects will be asked to empty their bladder right before the start of the scan (i.e., 1 h post injection). The patient will be in supine position during scanning. The total scanning procedure will take about 1 h.

First, the carotid bifurcation will be identified by means of MR angiography without contrast agent enhancement. Subsequently, transverse images will be obtained around the carotid bifurcation, so that the complete plaque will be imaged for all patients. A multi-sequence MRI protocol will be used, including a dark blood T1 and a bright blood sequence to assess the juxtaluminal calcifications, a hyper T1 weighted sequence for intra-plaque hemorrhage, and a post-contrast dark blood T1 weighted sequence to assess the lipid-rich necrotic core and fibrous cap status. Concomitantly with the MRI, a static PET scan will be performed. The total PET/MRI examination time will take approximately 1 h.

Images derived from the PET/MRI will be used to determine the uptake of Na[^18^F]F, which is well known to sensitively reflect the degree of vascular calcification. Secondly, the MRI images will serve for evaluation of the carotid artery morphology. For this purpose, a contrast agent (i.e., Gadobutrol) is injected (dose 0.1 mmol/kg of body weight). This MRI contrast agent will be injected according to the standard medical practice of the Maastricht University Medical Center as described within the respective ODIN protocol.

#### 5.2.1. PET Image Evaluation

A certified nuclear medicine physician will evaluate all the PET images, which are corrected for attenuation based on the MRI data, unaware of all clinical information, outcome of the extensive MRI analysis. A dedicated fusion software (Syngovia, Siemens) will be used to analyze the PET images. Mean and maximum standard uptake values (i.e., SUVs) will be normalized for blood tracer activity by dividing them by the mean standard uptake value of blood as measured in the internal jugular vein, the superior vena cava, or the right atrium depending on the vessel wall of interest.

#### 5.2.2. MRI Evaluation

The MRI reader will be trained using an independent training set. This training set is developed to be able to identify all different plaque characteristics, which are scored during this study. The reader will have to independently score images in this independent training set that has been previously scored by a highly experienced reader, to determine the inter-observer agreement. If the inter-observer agreement is not good or not very good, then the reader will be further trained until he performs excellent reading of the training set (i.e., good or very good inter-observer agreement with the highly experienced reader). The MRI reader, blinded to the results from the other modalities and clinical data, will independently score carotid plaque characteristics on the MR Images (vessel wall and lumen area, size of lipid-rich necrotic core, and size of calcifications, fibrous cap status, and size of intra-plaque hemorrhage). All data will be entered in a common database and analyzed by the investigator, supervised by a statistician.

### 5.3. CAC Scan

Non-contrast enhanced CT (Somatom FORCE, Siemens Healthcare), which will determine the CAC score, will be obtained at baseline and at the end of the study visits. The scans will be made using standard procedure.

The patient will be in supine position with his/her arms raised above his/her head during scanning. In addition, he/she is required to hold his/her breath for several seconds. The total procedure will take about 2–3 min. The procedure described above is the standard scanning-method in this hospital. The CAC score will be determined by performing a non-contrast enhanced high pitch scan.

All images will be assessed in consensus between an experienced radiologist and cardiologist. In case of disagreement, consensus will be reached by reviewing findings jointly.

As with the PET and MRI images, all CT images will also be examined by dedicated radiologists for incidental findings, which then will be reported to the general practitioner of the patients. Patients who do not want to be informed about additional findings are not able to participate in this study.

### 5.4. US Examination

The US examination is performed with the Art-Lab system (Esaote/Pie Medical, Maastricht, The Netherlands). With the subject lying supine, both common carotid arteries are identified on a longitudinal US image. On both walls of the common carotid arteries, a double line pattern can be observed, consisting of the edges of the lumen-intima-transition and media-adventitia-transition. On the far wall of the common carotid artery, the intima-media thickness is measured as the distance between these two lines in micrometers.

Additionally, the following parameters are measured:gray-scale median of the intima-media thickness;gray-scale median of the plaque;adventitia-adventitia diameter;intima-intima diameter;plaque echolucency.

The total duration of this investigation is approximately 15 min.

### 5.5. Laboratory Assessments

At baseline and at the end of the study visits, blood-samples (after an overnight fast) will be obtained for the measurement of several different cardiovascular parameters and markers of calcification and vitamin K status. In addition, 7 mL will be stored for future research. In total, almost 25 mL of blood will be obtained per study-visit for blood analysis. Therefore, almost 50 mL per subject for the entire project.

Blood samples will be processed by the Biobank Maastricht within 1 h and stored at −80 °C until analysis. We will investigate whether an association between biomarkers and calcification exists in an experimental setting. Therefore, we do not intend to inform the subjects of the blood results.

The routine assessments will be:total cholesterol;LDL-cholesterol;HDL-cholesterol;triglycerides;creatinine;glucose;albumin;parathyroid hormone;calcium;phosphate;coagulation function (e.g., PT, INR).

Specific laboratory assessments will consist in measuring the dp-ucMGP blood level.

## 6. Randomization, Blinding, and Treatment Allocation

A custom-made software with minimization as a randomization method (i.e., operated by the researcher) will randomize consecutive patients in the two arms, using the carotid stenosis as a stratification factor. The software will stratify the subjects according to the initial carotid stenosis into one of the following groups: stenosis 25–50% or stenosis > 50%. This software will assign subjects with a specific randomization number. This randomization number will be used by NattoPharma (Oslo, Norway) for coding and labelling of the capsule bottles. The list with all the randomization number will be stored in a secure location and will not be accessible for the investigators during this study.

The study code will be de-blinded if a serious adverse event occurs in an individual subject.

## 7. Investigational Product

Subjects in the intervention-group will receive a daily dose of 400 µg MK-7 and 80 µg vitamin D3. Each intervention capsule contains Cholecalciferol (per capsule: 1.6 mg of 1,000,000 UI/g; 1 UI of vitamin D = 0.025 μg) and MenaQ7 K2 oil (per capsule: 133.33 mg of 1500 ppm vitamin K).

MenaQ7 K2 oil is a synthetic MK-7 oil produced by NattoPharma (Oslo, Norway). Euro-Pharma Alliance Sp. zo.o. (Rzeplin, Poland) uses this oil to manufacture the capsules, which are later marketed by TG Montgomery AS (Oslo, Norway). TG Montgomery AS also distributes them as a food supplement on the Norwegian over-the-counter market. MenaQ7 is Generally Recognized as Safe (i.e., GRAS) by the U.S. Food and Drug Administration (i.e., FDA).

Both MK-7 and vitamin D3 are registered as food-supplements. MK-7 is well tolerated and does not cause a state of hypercoagulability [32]. There are no reported negative side effects associated with the use of MK-7 or vitamin D3, at the concentrations used in this study.

Subjects in the placebo-group will receive a capsule that is identical to the MK7+D3 one, but that does not contain any active substances. In all other aspects (e.g., shape, taste, weight, additives), this capsule is similar to the MK7+D3 one. The shell of both type of capsules is the same and compared to the MK-7+D3 ones, the placebos only contain bulking agent (the same one, i.e., linseed oil) in a higher amount, so that both capsules have the same weight. There are no reported negative side effects with the use of this placebo.

Both capsules are provided by TG Montgomery as a complete end-product ready to use and packaged separately for each participant in bottles. They are stored according to the manufacturer recommendation, which has already tested the shelf life and recommended a maximum storage time. This information will also be given to the subjects and they may request at any time a bottle replacement, in case of improper storage or passing the recommended maximum storage time.

